### Endpoint adjudication

A clinical event committee (CEC) blinded to treatment allocation will independently adjudicate the clinical events. The DSMB blinded to treatment allocation will also independently evaluate safety during the study period. The DSMB will also assess the necessity for revision of the trial design and the validity for continuance of trial entry, and if needed, recommend issues for the chief investigator. The members of the CEC and DSMB consist of authorized cardiologists or endocrinologists with relevant expertise.

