### Randomization and treatment

Eligible patients with the appropriately signed informed consent will be randomized to either the canagliflozin or glimepiride groups at a ratio of 1:1 using the minimization method with biased coin assignment balancing for age (<65, ≥65 year), HbA1c level (<6.5, ≥6.5 %), and left ventricular ejection fraction (LVEF; <40, ≥40 %) at the time of screening [18, 19]. The trial is an open-label design, although the assessor(s) will be blinded to treatment randomization. The assessors will also be blinded to the primary end point, NT-proBNP level, by measurement at a central laboratory.

All participants receive the study drug for 24 weeks. Patients who are assigned to the canagliflozin group receive canagliflozin 100 mg once daily. The EMPA-REG OUTCOME trial reported small dose-dependent effects of empagliflozin (10 mg vs. 25 mg/day) on metabolic parameters. However, the two dose groups had similar hazard ratios for cardiovascular outcomes [13]. Some studies on canagliflozin showed that 100 mg/day had sufficient effects on metabolic parameters, while 300 mg/day was slightly more effective [14, 15, 20]. Importantly, only 100 mg/day is approved in Japan, and therefore the dose of canagliflozin is fixed at 100 mg/day in the canagliflozin group. Because of the possible risk of excess diuresis and subsequent dehydration by combined use of canagliflozin and diuretics, the dose of the diuretics may need to be reduced when necessary. Patients assigned to the glimepiride group are started at a dose of 0.5 or 1.0 mg once or twice daily. According to the individual’s glycemic control, the dose of glimepiride can be increased to 6.0 mg/day. For background therapy in both groups, participants who have been receiving any SGLT2 inhibitor other than canagliflozin need to discontinue it at the start of the washout period, for 4 weeks, prior to receiving the study drug, canagliflozin or glimepiride. While, participants who have been taking a sulfonylurea need to stop taking it in the canagliflozin group and need to change to glimepiride (if needed) in the glimepiride group at the initiation of the study drug (Additional file 1). Because of the possible risk of excess diuresis and subsequent dehydration by combined use of canagliflozin and diuretics, the dose of the diuretics may need to be reduced when necessary.

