### Safety

Based on the intention-to-treat entire population, safety will be checked by recording the following adverse effects throughout the duration of the study: hypoglycemia, genital infections, urinary tract infections, excess osmotic diuresis signs (increased urinary frequency, mouth dryness, or polyuria), and hypovolemic symptoms. A previous study has reported an increased prevalence of hypoglycemia with sulfonylureas than with canagliflozin [14]. We therefore need to pay careful attention to the development of hypoglycemia, especially in patients assigned to the glimepiride group, despite this drug being initiated at a low dose in the study. If the investigators confirm these adverse effects, the grade of severity, treatment, outcomes, and relationship to the study drug will be assessed. The criteria for withdrawal from the trial are listed in Table 3. In addition, the incident of withdrawal from the study will be reported promptly to the Data and Safety Monitoring Board (DSMB) by the trial organizer.

**Table 3 Tab3:** Discontinuance criteria

Severe hypoglycemia that needs some support by family members or medical care at medical settings
Seriously poor glycemic control such as ≥HbA1c 10.0 %
Diabetic ketoacidosis
Dehydration
Considered inappropriate to continue the study by investigators due to aggravation of primary disease or complications
Considered inappropriate to continue the study by investigators due to adverse side effects of the study drug
Offer for participation declined by participants
Considered inappropriate to continue the study by investigators due to some other reason

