Previous clinical trials in T2DM patients demonstrated that SGLT2 inhibitors are well tolerated by patients and exert favorable effects on BP and systemic metabolisms such as body fat loss, in addition to improving glycemic control [10–12]. Experimental studies using animal models have shown that SGLT2 inhibitors also reduce inflammation and oxidative stress in hepatic, renal, and cardiac tissues [47–50], and therefore presumably would have a protective effect on the CV system. These class effects would be expected to be highly advantageous for diabetic patients with increased CV risk, while the diuretic effects of SGLT2 inhibitors may also be potentially effective in CHF patients who require frequent administration of diuretic agents. However, there is no evidence clinical evidence on the clinical safety of SGLT2 inhibitors for heart failure, and it is possible excess intravascular fluid depletion may be exacerbated following administration of SGLT2 in patients with heart failure taking diuretics. Given this current status, it is necessary to assess the safety and efficacy of SGLT2 inhibitors for diabetic patients with CHF.

The results of the EMPA-REG OUTCOME trial showed that administration of empagliflozin significantly reduced CV adverse outcomes in T2DM patients with higher CV risk [13]. Compared to the placebo group, any cause of death including worsening of heart failure, was significantly lower in the empagliflozin group. In addition, a 35 % relative risk reduction in hospitalization for heart failure was observed in the empagliflozin group. Although a significant reduction in hospitalization for heart failure was clearly documented, participants with heart failure comprised only about 10 % of the trial population at baseline. Moreover, about 40 % of the participants were taking diuretics at baseline, and therefore how to use SGLT2 inhibitors in conjunction with diuretics was of great concern in the clinical management of these patients. Taken together, the therapeutic effects of SGLT2 inhibitors in specific patients with heart failure have yet to be established (Fig. 1). It is therefore necessary to assess the clinical safety and efficacy of SGLT2 inhibitors focusing on T2DM patients with CHF.

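### The DSMB is blinded to allocation while it must judge safety and continued entry, so it cannot attribute a safety imbalance to a drug, and cannot see one if its data are pooled

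*Protocol article*

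**What the plan says.** The section Endpoint adjudication sets up two bodies and blinds both. For the event committee: "A clinical event committee (CEC) blinded to treatment allocation will independently adjudicate the clinical events". For the board: "The DSMB blinded to treatment allocation will also independently evaluate safety during the study period". The next sentence widens the board's remit: "The DSMB will also assess the necessity for revision of the trial design and the validity for continuance of trial entry", with recommendations going to the chief investigator.

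The section Safety adds a reporting line: "the incident of withdrawal from the study will be reported promptly to the Data and Safety Monitoring Board (DSMB) by the trial organizer". It does not say whether the patient's arm is reported too. Table 3 counts dehydration, severe hypoglycemia and aggravation of the primary disease among the reasons for discontinuation.

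On masking, Randomization and treatment says: "The trial is an open-label design, although the assessor(s) will be blinded to treatment randomization". The limitations paragraph of the Discussion adds that data management and statistical analysis are done blind.

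The paragraph on trial organization refers oversight details to Additional file 4, which is not shown. For the roles of the DSMB and the event committee, however, it points back to Endpoint adjudication.

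**The concern.** An event committee classifies one case at a time, and knowing the arm could bias it. A DSMB asked whether recruitment should go on faces a different question: is one treatment doing harm relative to the other? That calls for a comparison between identified arms. The article gives both bodies the same blinding.

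This matters more here because the expected harms are not shared. Randomization and treatment names a "possible risk of excess diuresis and subsequent dehydration by combined use of canagliflozin and diuretics". The Discussion repeats the worry: "it is possible excess intravascular fluid depletion may be exacerbated following administration of SGLT2 in patients with heart failure taking diuretics". The Safety section asks for particular vigilance about hypoglycemia in the glimepiride group. The Discussion also says that clinical safety evidence for the class in heart failure is lacking. An independent board that cannot link an excess to a drug is poorly placed to act on these risks.

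**Working it through.** The article gives no figure to reproduce. The check is a comparison of texts, followed by an illustration.

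**Step 1: is the blinding stated, or is detail merely missing?** It is stated. Endpoint adjudication applies it to the DSMB explicitly, and the organization paragraph names that section as the source for the board's role.

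**Step 2: does another section relax it?** No section shown gives the board by-arm tables, coded-arm tables or a route to request unblinding. Equally, none says that its tables are pooled. Two readings therefore remain.

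| What the blinded DSMB receives | Can it see an imbalance? | Can it attribute it to a drug? |
|---|---|---|
| Pooled data | No | No |
| Coded groups A and B | Yes | No |

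Only the last column is certain from the text.

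**Step 3: what does pooling hide?** Inputs: 125 patients per group (Sample size estimation), so 250 in total. The event counts are assumptions; the article gives no event rates.

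- Pooled rate for 12 events: 12/250 = 4.8%, whatever the split.
- By arm, with a two-sided Fisher exact test on a/125 v (12 − a)/125:

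| Split of 12 | Rates by arm | p |
|---|---|---|
| 6 v 6 | 4.8% v 4.8% | 1.00 |
| 10 v 2 | 8.0% v 1.6% | 0.034 |
| 11 v 1 | 8.8% v 0.8% | 0.005 |

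- With 20 assumed events the pooled rate is 20/250 = 8.0%. Splits of 10 v 10, 13 v 7, 15 v 5, 16 v 4 and 18 v 2 give p = 1.00, 0.24, 0.034, 0.009 and 0.0002.

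The p values only show how far apart the splits lie; they are not proposed as stopping boundaries. In a pooled report every split within a row total looks the same. In a coded report the uneven splits are visible, but the drug behind the excess is not.

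**Step 4: what does blinding the board protect?** Treating physicians already know their own patients' arms. The primary endpoint has separate protection, through central-laboratory measurement and blinded data handling and analysis. A by-arm safety review confined to the DSMB disturbs neither.

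**The case against.** The strongest objection is to a claim that a reader might infer: that the board is unable to see any excess of harm in one arm. The article does not support that. It never says the DSMB gets pooled data, and coded group tables are compatible with blinding; an 11 v 1 split would be plain in them. This objection stands, and the point is limited accordingly.

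Second, the format of DSMB reports and any unblinding procedure are details that an article usually leaves to the full protocol or a charter, and Additional file 4 is not shown. Their absence is not criticised here. The stated blinding is, because the article does fix it.

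Third, blinding the board has a purpose. Open-label treatment unblinds sites to their own patients but gives nobody cumulative results by arm, and a body that may recommend design changes is safer from data-driven revision if it does not know allocation. This has some force. It argues for withholding NT-proBNP comparisons from the board, and less for withholding safety data.

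Fourth, there are case-level safeguards. Investigators, who know the arm, assess severity, outcome and relation to the study drug, and withdrawals go promptly to the DSMB. These help, but do not replace a comparison between arms.

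Finally, having the outsourced analysts produce by-arm tables would conflict with the Discussion's statement that data are managed and analysed blind. That stands, and it shapes the fix.

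**Conclusion.** The concern holds in limited form. The article blinds to allocation the board that must judge safety and continued entry, in an open-label trial with a safety aim and arm-specific named risks. On the text shown, the DSMB cannot attribute a safety imbalance to a drug. That it could not see one at all depends on its data being pooled, which is neither stated nor excluded.

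The size cannot be expressed as a bias or a loss of power. The 4.8% example rests on an assumed event count and shows only what a pooled view would conceal. The conclusion also assumes that no document outside the article grants the board access. The change should be made: it concerns patient protection and leaves the primary analysis untouched.

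**What to change.** In Endpoint adjudication, restrict mandatory blinding to the clinical event committee and the endpoint assessors. State that the DSMB reviews serious adverse events, cardiovascular events, withdrawals, hypovolemia and hypoglycemia by arm in closed session or, at minimum, by coded arm with a right to unblind on request.

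Have the tables prepared under the existing contract by someone outside the blinded analysis team, and amend the Discussion's statement on blinded data handling to allow this. The Steering Committee and trial analysts stay blinded. The board is shown no NT-proBNP comparison, so no alpha is spent.

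The cost is a short change to the two sections and to any DSMB charter, minor work to separate the unblinded table preparation, and a small confidentiality risk contained by the closed session. If Additional file 4 or a charter already provides such access, the only change needed is to bring Endpoint adjudication into line with it.

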### Statistical considerations

#### Sample size estimation

Due to the lack of data on the effect of SGLT2 inhibitors, including canagliflozin, on NT-proBNP levels, we used data from the PARAMOUNT study on CHF patients with preserved ejection fraction [25]. That study used the same primary end point to compare the efficacy and safety of LCZ696, an angiotensin receptor neprilysin inhibitor, with valsartan. On the basis of the findings of that study, we assumed an 18 % difference in NT-proBNP reduction between the two groups in our trial. In detail, estimation of the sample size for the CANDLE trial was based on the percentage change from baseline to the final NT-proBNP level, required to demonstrate non-inferiority of canagliflozin versus glimepiride, using a one-sided Student t test with a 2.5 % type I error. In this calculation we assumed that for a common standard deviation for the log-scale of the ratio of 0.80, a clinical non-inferiority margin of 1.1, and a dropout rate of 10 %, it was necessary to recruit 125 patients in each group in the full analysis set (FAS) to demonstrate non-inferiority if the true difference was 18 % and the power was at least 80 %.

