### Trial population and recruitment

We aim to recruit a total of 250 participants across approximately 35 sites in Japan. Recruitment for this trial began in October 2015 and will be completed by December 2017. Eligible patients in the trial are T2DM patients with CHF (aged ≥20 years) who comply with all the enrollment criteria. The detailed inclusion and exclusion criteria are listed in Table 1. Briefly these criteria include: (1) Patients with appropriately diagnosed T2DM, who are drug-naïve or taking any anti-diabetic agent; (2) T2DM clinically requiring a start or change of an anti-diabetic agent; (3) complicating NYHA functional classification I to III CHF, but not IV, with maintenance of the clinical condition and unchanged medical treatment for CHF, including angiotensin-converting enzyme inhibitors, angiotensin II receptor blockers, beta-blockers, and diuretic agents for 4 weeks prior to screening. In the trial, CHF is classified comprehensively by skilled cardiologists using several findings, including clinical symptoms (the Framingham criteria for congestive heart failure and NYHA functional classification), history of hospitalization for heart failure, and clinical tests such as echocardiography and biomarkers. However, there is no limitation on the NT-proBNP level at enrollment. Prior to eligibility screening, every participant is required to receive an adequate explanation based of the trial plan, with written informed consent then being obtained from each patient.

**Table 1 Tab1:** Detailed inclusion and exclusion criteria

Inclusion	Exclusion
Adults (aged ≥20 years)	Type 1 diabetes mellitus
T2DM patients who need to start or who are possibly changing or adding an anti-diabetic agent	History of diabetic ketoacidosis, diabetic coma, or hypoglycemic attack ≤6 months prior to informed consent
CHF (NYHA functional classification I to III)	Severe renal dysfunction (eGFR <45 ml/min/1.73 m^2^) or patients receiving dialysis
Without change in NYHA functional classification or drugs for heart failure 4 weeks prior to eligibility	Severe liver dysfunction (at least threefold higher AST or ALT more than the upper limit of the facilities reference value
The patient provided written informed consent to participate in the study	CHF (NYHA functional classification IV)
	Patients with pituitary or adrenal dysfunction
	Patients with malnutrition, starvation, irregular eating pattern, lack of dietary intake, or debilitation

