#### Analysis plan

The analyses of the primary and secondary endpoints will be performed in the FAS, which includes all patients who received at least one dose of treatment during the study period and did not have any serious violation of the study protocol, and had data collected after commencement of treatment. For the baseline characteristics, the summary statistics will comprise frequencies and proportions for categorical variables, and means and standard deviations for continuous variables. The patient characteristics will be compared using Chi square tests for categorical variables, and t tests for normally distributed continuous variables or Wilcoxon rank sum tests for continuous variables with a skewed distribution.

For the primary analysis comparing treatment effects, the least square mean and its 95 % confidence interval will be estimated using analysis of covariance (ANCOVA). To test for non-inferiority of the primary endpoint, the ANCOVA will be applied adjusted for age (<65, ≥65 year), HbA1c level (<6.5, ≥6.5 %), and left ventricular ejection fraction (LVEF; <40, ≥40 %). The secondary analysis will be performed in the same manner as the primary analysis.

All comparisons are planned and all *p* values will be two sided. *P* values <0.05 will be considered statistically significant. All statistical analyses will be performed using SAS software version 9.4 (SAS Institute, Cary, NC, USA). The statistical analysis plan will be developed by the principal investigator and a biostatistician before completion of patient recruitment and database lock.

Trial organization and oversight (details in Additional file 4).

Principal investigators of the CANDLE trial are [name] (Chief), Department of Cardiovascular Medicine, Saga University and [name], Department of Cardiology, Nagoya University Graduate School of Medicine. The Steering Committee will carry out planning, operating, analyzing, and presentation of the trial. The Executive Committee will supervise the trial design and operation of the study. The roles of DSMB and CEC are described in the section of Endpoint adjudication. The trial secretariat is in DOT INTERNATIONAL CO., LTD, Tokyo, Japan. Each of data management, monitoring, statistical analyses, and audit will be independently implemented on the basis of outsourcing agreement.

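### The sample size paragraph uses 125 per group as both the recruited and the analysed number; if 125 are randomised, power on the stated inputs is about 78%, just under the claimed 80%

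*Protocol article*

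**What the plan says.** All the inputs are in the protocol article, under Sample size estimation:

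- Test and error rate: "using a one-sided Student t test with a 2.5 % type I error".
- Variability: "common standard deviation for the log-scale of the ratio of 0.80".
- Margin and loss: "a clinical non-inferiority margin of 1.1, and a dropout rate of 10" per cent.
- Effect and target: "if the true difference was 18 % and the power was at least 80" per cent.
- Result: "it was necessary to recruit 125 patients in each group in the full analysis set (FAS) to demonstrate non-inferiority".

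Under Trial population and recruitment the target is "We aim to recruit a total of 250 participants across approximately 35 sites in Japan", and the Abstract gives 250 as the number to be randomised. Under Randomization and treatment, patients are "randomized to either the canagliflozin or glimepiride groups at a ratio of 1:1", so 250 means 125 per group at randomisation.

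Under Analysis plan, the FAS is limited to treated patients who "did not have any serious violation of the study protocol, and had data collected after commencement of treatment". It is therefore a subset of those randomised.

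**The concern.** The result sentence joins two different counts. Recruiting 125 per group agrees with the total of 250. Placing those 125 in the FAS does not, because the same sentence allows for 10% loss. A reader cannot tell whether 125 already includes the dropout allowance or still has to be inflated.

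The answer decides which other statement gives way. If 125 is the randomised number, the power claim should be checked against the smaller number that remains. If 125 is the analysed number, the recruitment total is too low. The statistical analysis plan is still to be developed according to the Analysis plan section, and it should not inherit a sentence with two meanings.

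**Working it through.** **Inputs.** From Sample size estimation: SD of the log ratio 0.80, margin 1.1, one-sided alpha 0.025, power 0.80, dropout 10%. The 18% is read as a true ratio of 0.82 (canagliflozin to glimepiride). The article does not spell this out. It is the natural counterpart of a margin given as a ratio and an SD given for the log of the ratio.

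**Step 1. Distance from the truth to the margin, log scale.**

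ln(1.1) − ln(0.82) = 0.0953 + 0.1985 = 0.2938

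**Step 2. Trying to reproduce 125.** Normal approximation:

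n per group = 2 × (1.96 + 0.8416)² × 0.80² / 0.2938² = 116.4, so 117

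The exact noncentral t, which matches the stated test, gives 118.

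Inflating for dropout:

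- 117 / 0.9 = 130 per group (260 in total)
- 118 / 0.9 = 131.1, so 132 per group (264 in total)
- multiplying by 1.1 instead: 117 × 1.1 = 128.7, so 129; 118 × 1.1 = 129.8, so 130

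The stated 125 is neither the figure before inflation (117 or 118) nor the figure after it (129 to 132).

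**Step 3. If 125 per group are randomised.**

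125 × 0.9 = 112.5, so 112 to 113 analysed per group, about 225 in total

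Standard error = 0.80 × √(2/112.5) = 0.1067, and 0.2938 / 0.1067 = 2.754. The normal approximation gives power Φ(2.754 − 1.960) = 78.6%. The exact t gives 78.1% at 112 per group and 78.5% at 113.

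The 80% target is met only if at least 118 of the 125 are analysed, which is a loss of at most 7/125 = 5.6%, not 10%.

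**Step 4. If 125 per group is the FAS number.**

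Power is 82.4% by the exact t (82.7% by normal approximation), so the power claim is met. Recruitment is not: 125 / 0.9 = 138.9, so 139 per group, or 278 in total against 250.

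**Step 5. A possible source of 125.** Suppose the margin was entered as 0.10 on the log scale instead of ln(1.1) = 0.0953. The distance becomes 0.10 + 0.1985 = 0.2985, and

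2 × (1.96 + 0.8416)² × 0.80² / 0.2985² = 112.8, and 112.8 / 0.9 = 125.3

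That is close to 125, and 113 × 1.1 = 124.3 rounds up to 125. The stated t test, however, needs 114 analysed, or 114 / 0.9 = 126.7, so 127 randomised. At 112 to 113 analysed, it gives 79.4% to 79.7%.

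**The case against.** The strongest reply is that the intent is clear. Two other places give 250 as the number recruited or randomised, and the result sentence itself speaks of recruiting and follows a list that includes the dropout rate. On that view 125 is already inflated, the reference to the FAS is a misplaced phrase, and what remains is a gap of 1.5 to 2 points that may come only from rounding the log margin.

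Much of this stands. It is the more natural reading, and the fix below adopts it. The shortfall is small: 7 randomised patients per group by the t test, or 5 by the normal approximation. The rounded margin is a plausible explanation, although the article does not say it was used.

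The reply does not rescue the sentence as written. On its own reading the article promises at least 80%, and its printed inputs give about 78%. Even the rounded margin leaves the stated t test just under 80%.

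A reader might go further and infer that the trial both misses its power and under-recruits. The documents do not support that, because the two faults belong to alternative readings of 125 and only one can apply.

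**Conclusion.** The paragraph is inconsistent and should be corrected, but the effect on power is marginal. With 250 randomised and 10% lost, power is about 78% for a true ratio of 0.82, against a claim of at least 80%. With 125 per group in the FAS, power is about 82%, but the recruitment total falls 28 short (278 against 250). No reading satisfies the recruitment target, the dropout rate, the FAS count and the power claim together.

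This rests on two assumptions: that 18% means a ratio of 0.82, and that the 10% who drop out do not contribute to the primary analysis. If fewer are lost, power lies between the two figures.

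A reader might also infer a much larger deficit by taking the 18% as a log difference of 0.18 or as a ratio of 1/1.18. With 112 to 113 per group those readings give about 73% and 68%. They should not be taken as the size of the problem: they fit the ratio-based margin less naturally, and at the stated one-sided 2.5% neither reproduces 125 (they call for 147 to 149 and 163 to 166 randomised per group). They only show why the scale of the 18% should be written down.

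Nothing here affects the validity of the non-inferiority test. It concerns a stated design property and a count.

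**What to change.** Restate the sample size result along these lines:

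> 250 patients randomised (125 per group); with 10% dropout, about 225 in the FAS; power about 78% for a true geometric mean ratio of 0.82 against a margin of 1.1 (log SD 0.80, one-sided 2.5% t test).

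With it:

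- Remove the reference to the FAS from the figure of 125.
- State the 18% as a ratio and give its log value.
- Give the log margin actually used. If it was 0.10 and not ln(1.1), say so and report the power that follows from it.

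The change needs no extra patients and no change of design. Its cost is wording and a stated power slightly lower than the one now claimed. If the sponsor meant 125 per group in the FAS, the recruitment total must be reconciled with that instead, at about 278.
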